### **12.2 Participant demographics and other baseline characteristics**

Demographic and other baseline data will be listed and summarized descriptively by ethnicity and treatment group for the Safety set.

Categorical data will be presented as frequencies and percentages. For continuous data, mean, standard deviation (SD), median, minimum, and maximum will be presented.

Relevant medical histories and current medical conditions at baseline will be summarized jointly by system organ class, preferred term, ethnicity and by treatment group.

### **12.3 Treatments**

The Safety set will be used for the analyses below. Categorical data will be summarized as frequencies and percentages. For continuous data, mean, standard deviation, median, minimum, and maximum will be presented.

Concomitant medications and significant non-drug therapies prior to and after the start of the study treatment will be listed by treatment group, ethnicity, and participant. Summaries will be presented according to the Anatomical Therapeutic Chemical (ATC) classification system by ethnicity and treatment group.

### **12.4 Analysis of the primary endpoint(s)**

The primary objective of this study is to determine the safety, reactogenicity and tolerability of after single MIMIX MAP skin immunization in healthy adults. All safety summaries will be performed on the safety analysis set by ethnicity.

#### **12.4.1 Definition of primary endpoint(s)**

All safety data, including vital signs, laboratory parameters, AE, local and systemic reactogenicity events, physical exams are considered primary endpoints.

#### **12.4.2 Statistical model, hypothesis, and method of analysis**

For all safety analyses, the safety data set will be used. All listings will be presented by treatment group ethnicity, participant and visit/time (if applicable). Summaries will be presented by treatment group, ethnicity and visit/time (if applicable), with placebo data being pooled.

#### **Adverse events**

All information obtained on AEs will be displayed by treatment group, ethnicity, and participant.

The number (and percentage) of participants with treatment-emergent AEs (events started on or after the dose of study medication or events present prior to start of treatment but increased in severity on or after the dose of study medication based on preferred term) will be summarized in the following ways:

- by treatment, ethnicity, primary system organ class and preferred term.
- by treatment, ethnicity, primary system organ class, preferred term and maximum severity

Separate summaries will be provided for study medication related AEs, death, SAEs, other significant AEs leading to discontinuation.

A participant with multiple AEs within a primary system organ class is only counted once towards the total of the primary system organ class.

#### **Vital signs**

All vital signs data will be listed by treatment group, ethnicity, participant, and visit/time and if ranges are available, abnormalities will be flagged. Summary statistics will be provided by treatment group, ethnicity, and visit/time.

#### **Clinical laboratory evaluations**

All laboratory data will be listed by treatment group, ethnicity, participant, and visit/time and if normal ranges are available abnormalities will be flagged. Summary statistics will be provided by treatment group, ethnicity, and visit/time. Shift tables using the low/normal/high/ (low and high) classification will be used to compare baseline to the worst on-treatment value.

#### **Other safety evaluations**

All listings deemed relevant, including reactogenicity, physical examination, will be presented by treatment group, ethnicity, participant and visit. Summary statistics deemed relevant will be provided by treatment group, ethnicity and visit.

### **12.5 Analysis of secondary endpoints**

#### **12.5.1 Efficacy and/or immunogenicity endpoint(s)**

All immunogenicity data will be listed by treatment group and timepoint.

### 12.5.2 Safety endpoints

Not applicable.

### 12.5.3 Immunogenicity

Although clinical efficacy trials of new influenza vaccines may be performed in late-stage development or post-licensure, FDA licensure can be achieved based upon antigen specific HAI titers. The primary immunogenicity analyses will assess HAI GMTs, GMT mean fold rise, seroconversion rates (defined as a fourfold rise in HAI titers) and seroprotection status (defined as an HAI titer of  $\geq 1:40$ ), by HAI.

HAI antibodies in serum will be determined at specific time points for all participants, including the placebo group and all immunogenicity results will be listed by treatment group, ethnicity, participant and visit/time. Summary statistics may be provided as appropriate in case of high incidence of positive participants/samples.

Sera analyzed for determination of HAI titers will be evaluated as follows:

- Calculation of the geometric mean of pre- and post-vaccination HAI titers for each treatment group.
- Change from pre- to post-vaccination in geometric mean HAI titers for each treatment group.
- Seroconversion rate defined as percentage of participants with either a pre-vaccination HAI titer  $< 1:10$  and post vaccination HAI titer of  $\geq 1:40$  or a pre-vaccination HAI titer of  $\geq 1:10$  and a minimum four-fold rise in post vaccination HAI antibody titer at each timepoint.
- Seroprotection rate defined as the percentage of participants with a HAI titer  $\geq 1:40$  at each timepoint for the vaccine H1 strain

Incidence of positive participants and correlation with selected AEs and clinical outcomes may be explored as appropriate in case of high incidence.

## 12.6 Analysis of exploratory endpoints

Exploratory analyses will include evaluations of seroprotection status (defined as an HAI titer of  $\geq 1:40$ ), H1 virus microneutralization titers, GMT of H1 HA specific IgG, total IgE titers, GMT of silk fibroin specific IgG and HAI titer against against a drifted H1 strain. These endpoints will be assessed on (vaccination day), and on Days 29 ( $\pm 1$ ), and 180 ( $\pm 5$ ).

Sera analyzed for determination of HAI, serum anti-H1 HA IgG, virus microneutralization titers, total serum IgE and anti-silk fibroin by ELISA results will be evaluated as follows:

- Calculation of the geometric mean of pre- and post-vaccination HAI titers for each treatment group for a drifted H1 strain.
- Calculation of the geometric mean of pre- and post-vaccination anti-H1 IgG serum antibody titers for each treatment group for the vaccine H1 strain.

- Change from pre- to post-vaccination in geometric mean anti-H1 IgG for each treatment group for the vaccine H1 strain.
- Calculation of the geometric mean of pre- and post-vaccination anti-silk fibroin IgG serum antibody titers for each treatment group.
- Change from pre- to post-vaccination in geometric mean anti-silk fibroin IgG titers.
- Calculation of the geometric mean of pre- and post-vaccination total serum IgE titers
- Change from pre-to post-vaccination in geometric mean total IgE titers

### **12.7 Interim analyses**

An interim analysis will be conducted once all enrolled participants have completed Day 57 assessments or End of Study Visits or have withdrawn or are lost to follow-up.

### **12.8 Sample size calculation**

The primary objective of this FIH study is to assess the safety, reactogenicity and tolerability of VX-103. A sample size of 30 participants on active treatment (with additional 15 placebo participants) is consistent with historical clinical practice in similar studies.

## **13 ETHICAL CONSIDERATIONS AND ADMINISTRATIVE PROCEDURES**

### **13.1 Regulatory and ethical compliance**

This clinical study was designed and shall be implemented, executed and reported in accordance with the ICH Harmonized Tripartite Guidelines for Good Clinical Practice, with applicable local regulations (including European Directive 2001/20/EC, US CFR 21), and with the ethical principles laid down in the Declaration of Helsinki.

### **13.2 Responsibilities of the investigator and IRB/IEC**

Before initiating a trial, the investigator/institution must obtain approval/favorable opinion from the Institutional Review Board/Independent Ethics Committee (IRB/IEC) for the trial protocol, written ICF, consent form updates, participant recruitment procedures (e.g., advertisements) and any other written information to be provided to participants. Prior to study start, the investigator is required to sign a protocol signature page confirming his/her agreement to conduct the study in accordance with these documents and all of the instructions and procedures found in this protocol and to give access to all relevant data and records to Vaxess or designate's monitors, auditors, Quality Assurance representatives, designated agents of Vaxess, IRBs/IECs, and regulatory authorities as required. If an inspection of the clinical site is requested by a regulatory authority, the investigator must inform Vaxess and designate immediately that this request has been made.

### **13.3 Publication of study protocol and results**

This study only involves healthy volunteers and as such Vaxess will register the protocol as required to databases specified by local regulations. After study completion and finalization of the study report, results of this trial may be submitted for publication (e.g. peer-reviewed journal) or registered to databases where required by local regulations.

### **13.4 Quality Control and Quality Assurance**

Vaxess and/or designate maintains a Quality Management System (QMS) that includes all activities involved in quality assurance and quality control, to ensure compliance with written Standard Operating Procedures as well as applicable global/local GCP regulations and ICH Guidelines.

Audits of investigator sites, vendors, and Vaxess or designate may be performed by auditors, independent from those involved in conducting, monitoring or performing quality control of the clinical trial. The clinical audit process uses a knowledge/risk-based approach.

Audits may be conducted to assess GCP compliance with global and local regulatory requirements, protocols and internal SOPs, and are performed according to written Vaxess and/or designate's processes.

## **14 PROTOCOL ADHERENCE**

This protocol defines the study objectives, the study procedures and the data to be collected on study participants. Additional assessments required to ensure safety of participants should be administered as deemed necessary on a case-by-case basis. Under no circumstances including incidental collection is an investigator allowed to collect additional data or conduct any additional procedures for any purpose involving any investigational drugs under the protocol, other than the purpose of the study. If despite this interdiction prohibition, data, information, observation would be incidentally collected, the investigator shall immediately disclose it to Vaxess or designate and not use it for any purpose other than the study, except for the appropriate monitoring on study participants.

Investigators ascertain they will apply due diligence to avoid protocol deviations. If an investigator feels a protocol deviation would improve the conduct of the study this must be considered a protocol amendment, and unless such an amendment is agreed upon by Vaxess or designate and approved by the IRB/IEC and Health Authorities, where required, it cannot be implemented.

### **14.1 Protocol amendments**

Any change or addition to the protocol can only be made in a written protocol amendment that must be approved by Vaxess, health authorities where required, and the IRB/IEC prior to implementation.

Only amendments that are required for participant safety may be implemented immediately provided the health authorities are subsequently notified by protocol amendment and the reviewing IRB/IEC is notified.

Notwithstanding the need for approval of formal protocol amendments, the investigator is expected to take any immediate action required for the safety of any participant included in this study, even if this action represents a deviation from the protocol. In such cases, Vaxess should be notified of this action and the IRB/IEC at the study site should be informed according to local regulations.

## APPENDICES

### Appendix 1: Local Tolerability Scoring

Local tolerability scoring is adapted from the 2007 Food and Drug Association (FDA) Healthy Adult and Adolescent Volunteers Enrolled in Preventive Vaccine Clinical Trials (FDA, 2007) for assessment of Vaxess's 1 cm square MAP .

| Local Reaction to Product | Grade 0                | Mild (Grade 1)                                | Moderate (Grade 2)                                                                | Severe (Grade 3)                                             | Potentially Life Threatening (Grade 4)       |
|---------------------------|------------------------|-----------------------------------------------|-----------------------------------------------------------------------------------|--------------------------------------------------------------|----------------------------------------------|
| Pain                      | Pain is absent         | Does not interfere with activity              | Repeated use of non-narcotic pain reliever > 24 hours or interferes with activity | Any use of narcotic pain reliever or prevents daily activity | Emergency room (ER) visit or hospitalization |
| Tenderness                | No discomfort to touch | Mild discomfort to touch                      | Discomfort with movement                                                          | Significant discomfort at rest                               | ER visit or hospitalization                  |
| Erythema/Redness*         | <1 cm                  | 1– 5 cm                                       | 5.1 – 10 cm                                                                       | > 10 cm                                                      | Necrosis or exfoliative dermatitis           |
| Induration/ Swelling **   | <1 cm                  | 1 – 5 cm and does not interfere with activity | 5.1 – 10 cm or interferes with activity                                           | > 10 cm or prevents daily activity                           | Necrosis                                     |

\*In addition to grading the measured local reaction at the greatest single diameter, the measurement should be recorded as a continuous variable.

\*\* Induration/Swelling should be evaluated and graded using the functional scale as well as the actual measurement.

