|  | 
 
○ Standard descriptive demography. All participants who receive any investigational product will be included in the safety analyses.
 
○ Proportion of participants in each treatment group with any non-zero report will be tabulated for each local and systemic solicited and unsolicited reactogenicity event; groups will be compared by Fisher's exact test (alternatively, a Cochran-Mantel-Haenszel [CMH] test will be used to analyze events by ordinal severity category).
 
○ Participants with adverse events (including clinical laboratory abnormalities) will be summarized by Medical Dictionary for Regulatory Activities (MedDRA) body organ system and preferred term, severity, relatedness and, separately, by seriousness.
 
○ Proportion of participants in each treatment group with AE reports within each body organ system will be compared in the same manner. Significant heterogeneity will be probed at the preferred term level.
 
 
b) Immunogenicity Parameters
 
 
○ Sera collected will be analyzed for determination of HAI titers. Serum IgG anti-H1 HA, virus microneutralization titers, serum IgE and anti-silk fibroin by Enzyme-linked immunosorbent assay (ELISA) will be assessed on (vaccination day), and on Days 29 (<math>\pm 1</math>), and 180 (<math>\pm 5</math>).
 
 
The results of these determinations will be evaluated as follows:
 
 
● Calculation of the geometric mean of pre- and post-vaccination HAI and anti-H1 HAI IgG serum antibody titers for each treatment group.
 
● Change from pre- to post-vaccination in geometric mean HAI and anti-H1 HAI IgG titers for each treatment group.
 
● Seroconversion rate defined as percentage of participants with either a pre-vaccination HAI titer <math>< 1:10</math> and post vaccination HAI titer of <math>\geq 1:40</math> or a pre-vaccination HAI titer of <math>\geq 1:10</math> and a minimum four-fold rise in post vaccination HAI antibody titer at each timepoint.
 
● Seroprotection rate defined as the percentage of participants with a HAI titer <math>\geq 1:40</math> at each timepoint
 
● Calculation of the geometric mean of pre- and post-vaccination influenza virus microneutralization titers
 
● Change from pre- to post-vaccination in geometric mean microneutralization titers
 
● Calculation of the geometric mean of pre- and post-vaccination anti-silk fibroin serum IgG antibody titers for each treatment group.
 
● Change from pre- to post-vaccination in geometric mean anti-silk fibroin IgG titers
 
● Calculation of the geometric mean of pre- and post-vaccination total serum IgE titers
 
● Change from pre-to post-vaccination in geometric mean total IgE titers
 
 |

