After the MAP has been removed, skin tolerability assessments ([Appendix 1: Local Tolerability Scoring](#)) including pain, induration, tenderness and erythema will be assessed 1 (±2), 30 (±5) and 60 (±5) minutes post-MAP removal. Other local tolerability assessments ([Appendix 2: Other Local Tolerability Scoring](#)) including bruising, itching, skin-flaking and pigmented coloration will be assessed 60 (±5) minutes post-MAP removal.

If erythema, bruising or induration  $\geq 1$  cm around the treatment site is present, the maximum diameter will be recorded.

The MAP application site will be photographed with the study specific iPhone 1 ( $\pm 2$ ), 30 ( $\pm 5$ ) and 60 ( $\pm 5$ ) minutes post-MAP removal and with the iPhone attached to the study specific DermLite Imaging system 60 ( $\pm 5$ ) minutes post-MAP removal. Please refer to the Imaging Instructions document for additional details.

During the follow up visits, tolerability assessments, photographs of the MAP application site and blood samples will be taken for safety and immunogenicity assessments per the Assessment Schedule [Table 5](#).

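### The 1 cm erythema cut-off lies at or below the patch's own footprint, so device-only redness can score Grade 1 in every arm and weaken the planned Fisher comparison with placebo

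*Protocol*

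**What the plan says.** Appendix 1 (Local Tolerability Scoring) describes its scale as adapted "for assessment of Vaxess's 1 cm square MAP". For "Erythema/Redness" the grades are: below 1 cm, Grade 0; 1 to 5 cm, Grade 1; 5.1 to 10 cm, Grade 2; above 10 cm, Grade 3. The erythema footnote calls for "grading the measured local reaction at the greatest single diameter" and says that, in addition, "the measurement should be recorded as a continuous variable".

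Induration/swelling uses the same size bands, with a functional criterion added (Grade 1 is "1 – 5 cm and does not interfere with activity"). It has its own footnote, which asks for both the functional scale and the actual measurement.

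Section 6.1.1 gives a second measuring rule, covering erythema, bruising and induration: "induration $\geq 1$ cm around the treatment site is present, the maximum diameter will be recorded". It does not say whether the skin under the patch is included.

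The Protocol Synopsis (Endpoint Parameters, safety) fixes the comparison: the proportion with "any non-zero report will be tabulated for each local and systemic solicited and unsolicited reactogenicity event", compared between groups by Fisher's exact test, or alternatively by a Cochran-Mantel-Haenszel (CMH) test on ordinal severity. Placebo is a patch of the same composition without antigen. Skin scores are taken at 1, 30 and 60 minutes after removal and on Days 2, 4 and 8. Erythema alone continues on Days 15, 29, 57 and 180.

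**The concern.** The Grade 0/1 boundary is the only one that the binary endpoint uses, and it sits at the size of the device. A spring-applied adhesive microneedle patch may leave a red square for some time after removal. If the redness fills the footprint, it measures 1.00 cm along a side and 1.41 cm along the diagonal. At the greatest diameter that is Grade 1, whether or not the tips carried antigen.

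Placebo participants wear the same device, so such marks would add events to all arms and pull the proportions together. The CMH alternative does little to restore the contrast: a 1.2 cm imprint and a 4.5 cm reaction are both Grade 1 erythema. Swelling of that size can move up only through its functional criterion.

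Local reactogenicity against placebo is part of the primary objective. What is at stake is whether an antigen-driven local reaction would be visible in the comparison the synopsis names, when the measurement that could show it is already collected.

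**Working it through.** **Plan's own figure.** Section 12.8 gives 30 active plus 15 placebo, which agrees with 15 + 15 + 15 = 45. It rests on historical practice, with no alpha, power or event rate, so there is no power figure to reproduce. Two-sided 0.05 is assumed below.

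**Step 1: geometry.** Patch side = 1.00 cm; diagonal = √(1² + 1²) = 1.41 cm. The cut-off of 1 cm equals the side and is 0.41 cm below the diagonal.

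**Step 2: a bound that needs no imprint rate.** Suppose every active participant scores. Then all non-events are on placebo, and the exact probability of that table is C(15,k)/C(N,k), where k is the number of placebo participants without an event.
- 15 v 15, placebo 10/15 (k = 5): 3003/142506 = 0.0211; two-sided p = 0.042.
- 15 v 15, placebo 11/15 (k = 4): 1365/27405 = 0.0498; two-sided p = 0.0996.
- 30 v 15, placebo 12/15 (k = 3): 455/14190 = 0.032; the opposite tail is more probable than this table and is not added, so p = 0.032.
- 30 v 15, placebo 13/15 (k = 2): 105/990 = 0.106.

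An excess over placebo is therefore out of reach at 0.05 once placebo reaches 11/15 (73%) pairwise or 13/15 (87%) pooled.

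**Step 3: Fisher power under assumed rates.** Let g be the true reaction rate beyond the footprint (assumed 10% placebo, 60% active) and f the rate of footprint redness of at least 1 cm, equal in all arms and independent of g. Then P(non-zero) = 1 − (1 − f)(1 − g). Exact binomial power of the two-sided Fisher test:

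| f | Placebo v active, non-zero | 15 v 15 | 30 v 15 |
|---|---|---|---|
| 0 | 10% v 60% | 74% | 91% |
| 50% | 55% v 80% | 17% | 35% |
| 80% | 82% v 92% | 4% | 14% |
| 90% | 91% v 96% | 0.5% | 6% |
| 100% | 100% v 100% | 0% | 0% |

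**Step 4: rank test on diameter, same rates.** Simulation of 3,000 trials per setting. Each participant's value is the larger of imprint and reaction, and participants with neither share one lowest value.
- No imprint: 84% (15 v 15).
- Imprint 1.0-1.41 cm and reaction 1.5-5 cm, so sizes do not overlap: 66-69% (15 v 15) and 82-84% (30 v 15) for f from 50% to 100%.
- Imprint 1-2.5 cm and reaction 1.2-3 cm, so sizes overlap widely: about 42% at f = 50%, falling to 23% at f = 100% (15 v 15).

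Rejection when the arms do not differ is about 4-5% at those imprint rates. All size ranges are assumed.

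**The case against.** Several counter-arguments have force.

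A reader might infer that the imprint will score in every participant and that the Fisher comparison cannot discriminate at all. The protocol does not support that. It gives no human or placebo imprint rate. Section 8.4.4 reports transient erythema and edema in minipigs without rate, size or split by antigen. Section 1.2 separates the microneedle array from its backing, so the reacting area may be smaller than the patch. At a 50% placebo rate with a universal active response, Fisher power (15 v 15) is still 94%. It is also inexact to call the cut-off smaller than the patch: that is true of the diagonal only.

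The wording in Section 6.1.1 about the area around the treatment site can be read as excluding the footprint. On that reading, footprint-only redness would not count. This stands as an ambiguity between Section 6.1.1 and Appendix 1, and raters at up to three sites could resolve it differently.

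The instruction that "the measurement should be recorded as a continuous variable" belongs to the erythema footnote. The point is therefore firmest for erythema, and extends to swelling only where a diameter is recorded.

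The primary objective is to describe, no test is powered, and near-equal redness in all arms would itself be a valid tolerability result for the device. Sections 12.4.2 and 12.4.2's reactogenicity paragraph already foresee summaries by visit, and the time window may be set in the statistical analysis plan. This lowers the priority. It does not remove the point, because the grade boundary, the non-zero rule and the test are all written in this protocol.

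Finally, the rank test's advantage depends on how far imprint and reaction sizes overlap. That is correct, and the range above shows it. In every setting examined, the rank test still does at least as well as Fisher.

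**Conclusion.** The point holds in limited form. The Grade 0/1 erythema boundary lies at or below the patch footprint, so device-only redness can count as an event in every arm, placebo included. This weakens the any-non-zero comparison by an amount that depends on an unknown imprint rate.

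Under assumed true rates of 10% v 60%, the loss runs from none (no imprint) to complete (universal imprint), with most of the power gone by a 50% imprint rate. Complete failure needs a very high placebo count, as Step 2 shows. The problem is greatest if the 1-60 minute readings enter a worst-score analysis; the synopsis does not say whether they do.

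Priority is low to moderate: the objective is descriptive and the diameter is collected, so the information is not lost. The change is still worth making because it costs little.

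**What to change.** 1. Add to the synopsis safety analysis, for erythema and for measured induration/swelling where a diameter is recorded, a Wilcoxon rank-sum comparison of the diameter: each dose v placebo and pooled active v placebo, with the Hodges-Lehmann difference and 95% CI.
2. Use each participant's maximum diameter from Day 2 onwards, and report the 1, 30 and 60 minute readings separately. A maximum over all post-dose times would bring the immediate device marks back in.
3. Give all reactions below 1 cm one tied lowest value, so that the analysis does not depend on whether smaller diameters were written down.
4. Keep the graded incidence as a descriptive table.
5. Reconcile Section 6.1.1 and Appendix 1 on whether the patch footprint is included in the measurement, and tell raters before the first participant is scored.

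Cost: wording only, with no new visits, data or participants. A small downside is that a difference in centimetres is less familiar to readers than an incidence; the retained grade table covers that.
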